## Abstract

**Background:**

Many studies have demonstrated positive effects of physical activity on children’s health such as improved cardiorespiratory function and decreased obesity. Physical activity has also been found to have positive effects on academic achievement and cognitive function. However, there are few high quality RCT studies on this topic at present and the findings remain controversial.

**Methods:**

This protocol describes cluster randomized controlled trials assessing the impact of school-based exercise intervention among children in Mongolia. The intervention consists of 3-min sessions of high intensity interval training combined with music implemented two times a week at school during study periods. The participants are children in the fourth grade in public elementary schools in the Sukhbaatar district in Ulaanbaatar, Mongolia. The participants are cluster randomized by school and allocated either to the intervention or control group. The primary outcome is academic achievement. Secondary outcomes are obesity/overweight, physical fitness function, lifestyle, mental health, and cognitive function.

**Discussion:**

This cluster-RCT is designed and implemented to assess the effectiveness of exercise intervention on academic achievement, cognitive function, and physical and mental health among school-age children in Mongolia. This study will provide evidence to promote physical activities among children in low- and middle- income countries.

**Trial registration:**

UMIN: UMIN000031062. Registered on 1st February 2018.

## Background

Physical inactivity is becoming an urgent health issue. Although physical inactivity is highest in developed countries, it is also on the rise among middle-income earners in developing countries including their children [1]; the WHO reported that 81% of adolescents aged 11–17 years worldwide had insufficient levels of physical activity. [1]

Previous studies demonstrated a strong relationship between physical inactivity and non-communicable diseases such as obesity, hypertension, diabetes, elevated blood lipids, heart attack, heart failure, stroke, and breast and colon cancers [1, 2]. Physical activity in childhood is crucial for the healthy development of musculoskeletal tissue, the cardiovascular system, neuromuscular awareness, and prevention of obesity and diabetes. [1, 3] Moreover, recent studies have suggested that physical activity contributes to improving brain function and mental health. [4–8] Several ongoing studies are focusing on the positive effects of physical activity in broader areas such as academic achievement, cognitive function, mental health, and social skills. [3, 6, 9–15]

Academic achievement is a composite measure of many different factors from the developmental to the psychosocial. Several mechanisms thought to be instrumental in improving academic achievement have been reported from the neurobiological, psychological, and physical perspectives. Neurobiologically, exercise induces increased cerebral blood flow, brain-derived neurotrophic factors, neuroplasticity, and changes in neurotransmitters such as serotonin, noradrenalin, and dopamine. [4, 5] For example, the acquisition of motor skills was shown to improve neuroplasticity and cognitive function, [5] and improvements in executive function, memory, and attention have been reported in connection with increased physical activity. [16–20] The executive function is considered to be especially important for predicting children’s academic achievement. [21] Psychologically, exercise is thought to improve mood, lessen anxiety, and boost self-perception/self-esteem, all of which contribute to better academic achievement. [3, 11, 22] Numerous studies have demonstrated the positive effects of exercise on academic achievement and cognitive function, but most were small randomized controlled trials (RCTs), and some were not intervention studies. [10, 16, 17, 23–26] To date there are very few, large, population-based RCT examining the effect of exercise in children. A small number of meta-analyses and systematic reviews have been done but have demonstrated only small positive effects due to exercise intervention. [8, 12, 27] A Cochrane systematic review recommended investigating academic achievement and brain function in obesity-prevention studies because only few RCT addressing these issue exist [28] and the current evidence is meager. High-quality RCT are needed especially in developing countries as most of the previous intervention studies were done in developed countries like the US, Canada, and Australia.

As studies of children in the developed world have shown, physical activity deficits among children not only result in increased obesity and poorer athletic ability but may also have adverse effects on academic achievement and brain function. Similar trends are now being seen among children in emerging nations. Mongolia is one of these emerging nations now facing an epidemiological transition from infectious diseases to non-communicable and lifestyle-related health issues. In Mongolia, the physical activity deficit among children has become a serious problem in recent years especially in Ulaanbaatar, the capital city, where the shortage of outdoor play spaces caused by rapid urbanization, the spread of television and video games, and severe winter weather, have reduced the physical activity levels of children. In Ulaanbaatar, the average temperature is below freezing for more than five months per year. This fact has contributed greatly to increasing child obesity. In Mongolia, previous studies showed that the rate of overweight and obesity was 10.6 and 1.5%, respectively, among children aged 12–17. [29] Physical inactivity and obesity cause childhood health problems including diabetes mellitus, hypertension, hyperlipidemia, etc. Moreover, the adverse effects of exercise deficits are thought to have non-physical consequences including poor academic achievement and cognitive development. These health problems are common to middle-income earners worldwide, including those in developing countries like Mongolia.

The primary objective of our study is to investigate the effectiveness of exercise intervention on academic achievement among children using a large cluster RCT. The secondary objective is to investigate the effectiveness of exercise intervention on reducing the prevalence of obesity and overweight and on improving physical fitness performance, lifestyle, mental health, and cognitive function. The executive function was chosen as the target cognitive function based on the hypothesis that this function can best predict academic achievement.

## Methods/design

This study will be a collaborative effort by the National Center for Child Health and Development, Mongolian National Institute of Physical Education (MNIPE), and the University of Tsukuba. This study is a cluster-RCT using school as a cluster. A pilot study has already been done to confirm the feasibility and logistics of the planned intervention program and the assessment of the subjects’ physical fitness and cognitive function at one school in the study area.

### The study setting

This study will be conducted in the Sukhbaatar district of Ulaanbaatar, Mongolia and will recruit 10 public schools out of 11 public schools in the district. The population of this district in 2017 was 136,569 or roughly 10% of the population of Ulaanbaatar. [30]

One school which is not recruited for this study participated in the pilot study. Ten schools will later be allocated to the intervention or control group. Six, three, and two schools are located in urban or residential, *ger* (Mongolian traditional dwelling), and mixed residential areas, respectively. Each school has a total of 108 to 307 children in four to nine fourth-grade classes.

### Participants

Participants are children in the fourth grade in public elementary schools in the study area. The inclusion criteria are: [1] attendance at a public school in the Sukhbaatar district; [2] written consent from parents or guardians; and [3] age-appropriate literacy in Mongolian. The exclusion criteria are: [1] comorbidities or contraindications prohibiting participation in an exercise program and [2] enrollment in a special needs program.

### Intervention

The exercise program for the intervention group will be implemented two times per week at school in twice-weekly physical education classes required by the educational curriculum. The exercise program combines high intensity interval training and music. The exercise program will consist of four segments with different target activities and short rest intervals between segment. The target activities of each segment are warm-up, agility and high-speed movements, side-steps, and jumps. The program requires 3 min. In the first phase of intervention, the participants will practice each segment one by one to synchronize their movements with the music. Including stretching and explanation of the program before the exercise program, it will take about 20 min. The first phase will last for six weeks. Subsequently, in the second phase of the intervention, the participants will perform all the segments sequentially. Including stretching, it will take 10 min. The second phase will last for four weeks.

The program, based on high intensity interval training (HIIT), will consist of high intensity phases involving steps, jumps, and squats alternating with intervals of rest. HIIT has been found to improve physical endurance effectively. Some studies using small samples have also reported that HIIT improved not only physical endurance but also cognitive function more efficiently to compare with moderate-intensity endurance training. [31–34] This exercise program uses music, sound effects and verbal instructions in Mongolian to help children, especially those who are poor at physical activities, to acquire the movement easily. For this purpose, the tempo of music is set at 105-140 bpm. The music is also chosen carefully to amuse and motivate children. [35, 36] This program does not use self-paced or acquired movements such as walking. Through this program, the participants will aim to acquire a variety of motor skills, which is thought to correlate with improvements in cognitive function. This intervention will be administered by university students at MNIPE working as research assistants (RA). The RA will undergo a five-day course covering the aims of the program, appropriate practices, safety measures including ensuring the health and well-being of the participants, and training in implementing the exercise regimen. The RA will be instructed using standardized materials at the course and receive a few days additional course to improve the quality of intervention program during the intervention period. This program will be implemented in a space available at each school, such as the gymnasium or conference room. Although practice is recommended at least two times per week, each school will decide the actual frequency. There are no criteria for discontinuing participation or modifying the allocation. During the study period, MNIPE researchers will visit schools in the intervention group on a regular basis and supervise implementation of the program. In the control arm, the participants will attend the usual physical education class only.

### Primary outcome

The primary outcome of academic achievement will be assessed by the participants’ performance on the examination in 2018, which consists of a mathematics and Mongolian language portion. The participants’ score on the test for May 2017 at the end of third grade will be used as the baseline data.

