The intervention will begin in April 2018. Randomized allocation is done in February 2018 and baseline data collection will be done from February to April 2018. The intervention period will be interrupted by summer vacation between the end of June and the beginning of September 2018. The intervention period before summer vacation is the first phase of the intervention and after summer vacation is the second phase of the intervention. Post-intervention data will be collected between November and December 2018. (Fig. 1).

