### Statistical methods

#### Analysis of the primary outcome

The baseline data of the intervention and control groups will be compared. The chi-squared test will be used for binary variables and the t-test will be used for continuous variables. To avoid overestimating the impact of the intervention, an intention-to-treat approach will be adopted to evaluate the impact on the primary and secondary outcomes. In this study, an individual’s data will be analyzed in the originally allocated arm even if the individual moves to a school in another area during study period.

To examine the effect of the intervention while taking the hierarchical structure into consideration, we will use a linear mixed effect model. In this model, the fixed effects are the group (intervention/control), site (Urban/ *ger* or mixed residential), and measurement time point with the following two interaction terms: the interaction between group and measurement time point, and the interaction between the group, measurement time point, and site. The random effects are school and individual. The degrees of freedom will be estimated using Satterthwaite approximation. For the primary analysis, we will compare the participants’ performance on the national year-end examination before and after the intervention using least squares means estimated by the interaction term of the group, measurement time point, and site. The Bonferroni method will be used as a multiplicity adjustment method. A significance level of 0.025 will be set for a two-sided test, and the 95% confidence interval will be calculated.

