#### Subgroup analysis

The effect of the intervention will be further analyzed using four subgroup analyses. The first subgroup analysis will focus on the location of the schools (urban and non-urban areas), the second on gender, and the third on baseline physical fitness performance using the median score on a 20m shuttle run. The fourth subgroup analysis will focus on baseline academic achievement using the total score on the national year-end examination in May 2017 and the median score. The fifth subgroup analysis will be done after excluding participants whose correct rate on the Flanker test is below 80% at either the baseline or endline surveys.

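### The protocol's dates for the primary exam conflict: a May year-end exam in 2018 would precede the second phase, and a November-December exam would not be the year-end exam used at baseline

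*Protocol article*

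**What the plan says.** All references are to the protocol article.

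- **Primary outcome:** the outcome is "performance on the examination in 2018, which consists of a mathematics and Mongolian language portion", with no month. For baseline, the "score on the test for May 2017 at the end of third grade will be used as the baseline data".
- **Subgroup analysis:** the baseline test is identified by name and date as "the total score on the national year-end examination in May 2017". The year-end in question is therefore the end of the school year, not of the calendar year.
- **Analysis of the primary outcome:** the confirmatory contrast compares the "national year-end examination before and after the intervention".
- **Secondary outcomes, schedule paragraph:** "The intervention will begin in April 2018". It is "interrupted by summer vacation between the end of June and the beginning of September 2018". The phases are split at that break: "The intervention period before summer vacation is the first phase of the intervention and after summer vacation is the second phase of the intervention". Collection of post-intervention data is set for November-December 2018. The secondary outcomes carry that window explicitly.
- **Intervention:** the first phase lasts six weeks, with segments practised one at a time. The second lasts four weeks, with all segments performed in sequence.

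**The concern.** The confirmatory endpoint is described in three ways that do not fit one calendar: as the same year-end exam as baseline, as a measure taken after the intervention, and as belonging to a trial whose second phase starts only in September 2018.

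What the primary result would mean is at stake. If the May exam is used, an outcome taken during the programme would be reported as post-intervention. The academic result would then reflect first-phase exposure at most, while fitness, BMI, mental health and Flanker results would reflect the whole programme. The two sets of results could not be read side by side as effects of the same intervention. If a later exam is used, the before-after comparison is between two different tests, which the analysis text does not acknowledge. The primary outcome is also the only outcome without a stated date in the text.

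**Working it through.** **Step 1. Calendar inputs.** Start: some day in April 2018. Summer break: end of June to beginning of September 2018. Phase lengths: 6 and 4 weeks, 10 in all. Post-intervention window: November-December 2018. Baseline exam: May 2017. Month of the 2018 exam: not stated.

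**Step 2. Reading A: the 2018 exam is in May, like its 2017 counterpart.**

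- Longest possible lead-in: 1 April to 31 May = 60 days = 8.6 weeks, capped at the six weeks of phase 1.
- Shortest: 30 April to 1 May = 1 day = 0.1 week.
- Programme weeks before the exam: about 0 to 6 of 10, so at most 60%.
- Second-phase weeks before the exam: 0 of 4.
- Gap from the exam to the earliest second-phase start, taken as 1 September: 93 days (13.3 weeks) from 31 May and 123 days (17.6 weeks) from 1 May.
- Gap to the post-intervention window: about 5 months (31 May to 1 November) to 8 months (1 May to 31 December).

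Under A the description of the exam as following the intervention is wrong.

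**Step 3. Reading B: the 2018 exam is in November-December.** It then follows the second phase, but it is not the end-of-school-year exam. Children who completed third grade in May 2017 would normally have completed fourth grade by mid-2018, so it would be sat in the next school year. Under B the year-end label, and with it the implied like-for-like comparison with baseline, is wrong.

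**Step 4. The plan's own power figures.** Table 1 comes from a mixed-model simulation, and the document gives no closed formula. A change-score approximation is

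power = Φ( δ / √(2(1−ρ)·2/n) − 2.241 ),

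where 2.241 is the two-sided 0.025 critical value and n is children per arm within a site group. The split by site is not stated. Solving the ρ = 0.5 row gives about 665 (urban) and 398 (ger or mixed). I use 668 and 400, for a total of 2 × (668 + 400) = 2136, against 2337 × 0.95 = 2220 after the stated dropout. With δ = 0.2:

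| ρ | Urban: computed / Table 1 | Ger or mixed: computed / Table 1 |
|---|---|---|
| 0.4 | 0.863 / 0.871 | 0.633 / 0.642 |
| 0.5 | 0.921 / 0.920 | 0.721 / 0.719 |
| 0.6 | 0.967 / 0.967 | 0.821 / 0.814 |

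All six cells agree within 0.01, so Table 1 is not in dispute.

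**Step 5. Illustration under Reading A, ρ = 0.5.** How the effect accrues is not in the document, so each line below assumes a scaling.

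- *Effect proportional to weeks, six of ten delivered:* δ = 0.6 × 0.2 = 0.12. Urban Φ(2.193 − 2.241) = 0.48. Ger or mixed Φ(1.697 − 2.241) = 0.29. At least one site: 1 − 0.519 × 0.707 = 0.63, against 0.977 in Table 1.
- *Effect proportional to session minutes at two sessions a week:* phase 1 is 6 × 2 × 20 = 240 minutes and phase 2 is 4 × 2 × 10 = 80, so 240/320 = 75% and δ = 0.15. Urban 0.69, ger or mixed 0.45, at least one site 0.83. These minutes include stretching and, in phase 1, explanation.

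The spread between the two lines shows how far the figure depends on the assumed scaling.

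**The case against.** The strongest reply is that May 2018 appears nowhere. The month is inferred from the 2017 exam, and Fig. 1, the schedule of assessments, is not shown and may date it. A journal article also condenses a fuller protocol, so a missing month alone is no fault. That stands: the absence of a date is not the point, and the text does not establish that the primary outcome is mistimed. What the reply does not remove is the conflict between statements that are present. If the figure says May, the words placing the exam after the intervention fail. If it says November-December, the year-end label fails.

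A second reply is that only one phrase in the analysis section is loose and everything else can be read consistently around it. This is largely fair, but the phrase defines the confirmatory contrast, and which half of it is wrong changes what the trial estimates.

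A reader might go further and infer that a null result on a May exam would say nothing about the intervention. The document does not support that. The first phase is six of the ten programme weeks, with longer sessions than the second, so a May result could inform on first-phase exposure, though not on the complete programme. A reader might also take the power figures as the expected loss. They rest on a scaling that the document does not give and on back-solved site sizes.

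**Conclusion.** The conflict is real and lies in the text. The named exam, its baseline month, its description as before and after the intervention, and the two-phase calendar cannot all be correct. The conclusion that one part must change does not depend on the unstated month.

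Its size, if the 2018 exam is in May: at most six of ten programme weeks and none of the four second-phase weeks precede the primary outcome, and the exam is some five to eight months earlier than the secondary measurements. That part rests on the inference that the year-end exam keeps its May date. If the exam is in November-December, exposure is complete and the 0.2 SD assumption is untouched, but the test differs from baseline. The power figures (about 0.48 and 0.29 at 0.12 SD, 0.69 and 0.45 at 0.15 SD, ρ = 0.5) are illustrative only. The matter should be settled before analysis because it determines what the primary result can be said to show.

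**What to change.** Reconcile Primary outcome, the schedule paragraph under Secondary outcomes, Analysis of the primary outcome, and Subgroup analysis by stating which 2018 exam is primary and when it is sat relative to the two phases. Then take whichever branch is true:

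- **If it is the May year-end exam:** state that the primary outcome measures first-phase exposure only, remove the description of it as following the intervention, and limit the conclusion on academic achievement accordingly.
- **If a common mathematics and language exam after the second phase exists in all ten schools:** name it as primary, drop the year-end label, and acknowledge that it is not the same test as baseline. The document mentions no such exam, so its existence must be confirmed first.

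The first branch costs only wording. The second costs wording plus confirmation, and possibly coordination with the schools, that one exam is used in all ten. Any power statement added should name its assumption about how the effect accrues.

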### Secondary outcomes

The proportion of obesity and overweight, and the physical fitness function, lifestyle, and mental health, and cognitive function measures between November and December 2018 will be the secondary outcomes. All measures will be obtained in between February and April in 2018 as baseline data.

The researchers and RAs will obtain physical measurements (height and body weight) and physical fitness function test data to establish the baseline in February and at the end of study. The body mass index (BMI) will be calculated, and the proportion of participants classified as obese or overweight using the WHO/CDC criteria will be calculated. Physical fitness function will be assessed by participants’ performance on a 20-m shuttle run and side-to-side jumps.

Participants’ parents or guardians will answer a self-administered questionnaire on lifestyle covering their children’s sleeping hours, exercise habits, time spent viewing television or using video games, children’s household tasks, and their mental and physical health. Children’s physical health condition will be assessed using a five-point Likert scale. The Strengths and Difficulties Questionnaire (SDQ), which has already translated into Mongolian and back-translated, [37] will be used to assess the mental health of the participants. The cut-off values on the SDQ published in the literature and available on the official website for ‘normal,’ ‘borderline,’ and ‘abnormal’ will be adopted. [38]

To assess cognitive function, the Flanker test, a representative cognitive function test specifically assessing inhibitory control of the executive function, will be used. [39] The Flanker test will be administered using a specially-designed app for use on a tablet at school under the instruction of the researchers. The response time and correct rate for 50 tasks, including congruent and incongruent tasks, will be measured. Before the actual test, every student will do a practice test consisting of ten tasks once or twice.

The intervention will begin in April 2018. Randomized allocation is done in February 2018 and baseline data collection will be done from February to April 2018. The intervention period will be interrupted by summer vacation between the end of June and the beginning of September 2018. The intervention period before summer vacation is the first phase of the intervention and after summer vacation is the second phase of the intervention. Post-intervention data will be collected between November and December 2018. (Fig. 1).

